### CFIR determinants

2.9

Although the primary focus of this study is evaluation of acceptability, feasibility, and adoption, selected domains of the Consolidated Framework for Implementation Research (CFIR) will be used to structure interpretation of implementation experience across recruiting facilities (Table 2). Given the standardized nature of the program and the emphasis on adherence to centrally defined SOPs, CFIR is applied in a focused manner to identify contextual factors that may influence fidelity and maintenance. Determinant data will be derived from routine program monitoring, structured provider surveys, notes from monthly quality assurance calls, and documentation of protocol deviations. This approach allows systematic interpretation of barriers and facilitators without introducing intensive qualitative data collection or additional burden to participating facilities focused on program implementation. CFIR constructs are therefore applied deductively as an interpretive lens rather than as the basis for inductive qualitative analysis; free-text survey responses will be summarized descriptively.

**Table 2 T2:** Selected CFIR domains used to interpret implementation feasibility and fidelity.

CFIR domain	Constructs	Data sources	Role in analysis
Intervention characteristics	Perceived complexity of ARF criteria; clarity of SOPs; registry usability	Provider structured surveys; frequency of protocol deviations; registry completeness	Explain fidelity variation
Inner setting	Leadership engagement; staffing capacity; competing clinical priorities	Monthly monitoring calls; structured surveys; site logs; documentation of workflow barriers	Interpret feasibility differences
Outer setting	Referral networks; geographic barriers	Referral source data; catchment descriptions; distance to facility	Contextualize reach
Characteristics of individuals	Provider knowledge; confidence in ARF diagnosis; perceived value of program	Provider surveys	Assess adoption, acceptability and sustained engagement
Implementation process	Training adequacy; quality assurance feedback; monitoring intensity	Cardiologist echo over-read reporting form; structured surveys; notes from monthly reviews	Examine mechanisms supporting fidelity

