### Objectives

1.1

The primary objective of the study described in this protocol is to assess the acceptability, feasibility and facility-level adoption of the described ARF case-finding and registry program embedded within routine district and referral hospital care across diverse geographic settings in Nepal. This study does not evaluate the clinical effectiveness of ARF case-finding or its impact on RHD outcomes, which are beyond the scope of this early implementation evaluation.

Secondary objectives are: to measure fidelity to standard operating procedures (SOPs), defined as adherence to ARF diagnostic criteria, echocardiographic protocols, and registry documentation requirements; to describe the penetration of ARF case-finding within participating facility catchment areas; to evaluate short-term sustainability, defined as continued program operation and sustained workflow adherence at 12 months; to identify contextual factors associated with variation in adoption and fidelity across KIOCH and referral facilities using selected Consolidated Framework for Implementation Research (CFIR) domains.

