Feasibility	Facility/provider	Can the standardized workflow be delivered within routine inpatient and outpatient care?	Reported workflow barriers Time burden estimates Documentation of contextual constraints	Monthly monitoring reports Provider structured surveys
Fidelity	Facility/provider	Are ARF diagnostic and registry procedures implemented according to centrally defined SOPs?	Proportion of evaluations meeting Jones criteria documentation standards Echocardiography completeness and image adequacy Registry completeness Frequency and nature of protocol deviations	REDCap clinical data Monthly monitoring reports
Sustainability	Facility	Is the program still operational with sustained adherence at 12 months?	Continued ARF case enrollment activity Continued registry use Ongoing participation in QA processes Sustained workflow adherence	REDCap clinical data Monthly monitoring reports
—	Patient/Facility	How is the standardized workflow functioning clinically during early implementation?	Number and proportion of ARF diagnoses among evaluated children Diagnostic concordance with central cardiologist review Time from symptom onset to diagnosis Time from diagnosis to initiation of prophylaxis Follow-up completion at 3, 6, and 12 months	REDCap clinical data Facility clinical records

Exploratory care-process indicators will be assessed at the patient level and are intended to characterize whether the intervention may function to improve ARF care in the absence of pre-implementation comparator data. These include the number and proportion of ARF diagnoses among evaluated children, accuracy and timeliness of diagnosis, linkage to follow-up care, and follow-up completion over time. These measures are descriptive and are not intended to evaluate long-term clinical effectiveness.

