### Analysis

2.10

Analyses will be descriptive and exploratory, consistent with the pragmatic, non-randomized design and primary focus on implementation outcomes. Acceptability, adoption, feasibility, fidelity, penetration, and short-term sustainability will be summarized at the facility level using appropriate summary statistics. Results will be reported individually by facility and stratified by facility type (district vs. referral hospital) to characterize variation in implementation experience across site types.

Acceptability will be assessed through a simple summary statistics including means, and ranges of scores from providers surveys, and through a quantifying data found in provider and hospital superintendent surveys.

Adoption will be assessed through a narrative description of how workflows were deployed across facilities using data from provider surveys, REDCap clinical records, and facility clinical records.

Feasibility will be assessed quantitively through the percentage of workflows that are completed using data from REDCap clinical records and qualitatively through barriers reported in the provider structured surveys and monthly monitoring reports.

Fidelity will be quantified using adherence metrics including completeness of RedCap registry forms, echocardiographic protocol compliance, and documented protocol deviations from monthly monitoring reports.

Short-term sustainability will be evaluated quantitatively based on continued case enrollment, REDCap registry use, and participation in quality assurance processes at 12 months using data from REDCap activity logs and monthly reports.

Exploratory care-process indicators will be summarized at the patient level, including diagnostic patterns, concordance with central review, timeliness of diagnosis, and follow-up completion. In cases where initial diagnosis is unclear and reclassification occurs, final diagnoses will be used where possible. These measures are descriptive and not intended to assess clinical effectiveness. The study is not designed for formal between-facility comparisons. Patient-level registry data, provider-level survey data, and facility-level monitoring reports serve complementary descriptive roles and are not formally integrated through multilevel modeling, consistent with the pragmatic, single-arm design.

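### Table 2, Intervention characteristics row: two of the three data sources offered to explain fidelity are themselves measures of fidelity, so that row's interpretation is circular

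*Protocol article*

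**What the plan says.** Section 1.1 (Objectives) sets a secondary objective "to identify contextual factors associated with variation in adoption and fidelity across KIOCH and referral facilities", using selected CFIR domains.

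The outcome side is fixed in two places. The Fidelity row of Table 1 (section 2.8) includes among its data elements "Registry completeness Frequency and nature of protocol deviations". Section 2.10 (Analysis) then states: "Fidelity will be quantified using adherence metrics including completeness of RedCap registry forms, echocardiographic protocol compliance, and documented protocol deviations from monthly monitoring reports".

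The explanatory side is fixed in section 2.9. In Table 2, the Intervention characteristics row covers the constructs "Perceived complexity of ARF criteria; clarity of SOPs; registry usability". Its data sources are "Provider structured surveys; frequency of protocol deviations; registry completeness" and its role in the analysis is "Explain fidelity variation". The text above the table adds: "Determinant data will be derived from routine program monitoring, structured provider surveys, notes from monthly quality assurance calls, and documentation of protocol deviations".

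**The concern.** A determinant can explain an outcome only if it is observed separately from that outcome. Here two of the quantities that tell the reader a facility has low fidelity are also listed as data on why its fidelity is low. Suppose a facility has many incomplete registry forms. Under Table 1 that is low fidelity. Under Table 2 the same incompleteness may be read as a sign that the registry is hard to use, and then given as the reason for the low fidelity. Nothing has been learned about the cause.

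The risk is misattribution. The Discussion expects staff turnover, uneven infrastructure and high patient volume to affect adoption and fidelity. Any of these could leave forms incomplete even if the registry is easy to use and the procedures are clear. Reading incompleteness as a property of the intervention would credit this row with effects that belong to the Inner setting row, and could point the sponsor towards rewriting procedures when the problem is staffing. Because section 2.10 sets no thresholds for success and relies on CFIR-identified context to interpret the outcomes, the quality of that interpretation matters.

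**Working it through.** The article gives no figure to reproduce, and no sample size or error rate bears on the point. The check sets the entries side by side and counts the overlap.

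**Fidelity elements in Table 1 (four):**
1. Documentation of the Jones criteria to standard
2. Completeness of echocardiography and adequacy of images
3. Registry completeness
4. Frequency and nature of protocol deviations

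**Fidelity metrics named in section 2.10 (three):**
1. Completeness of registry forms
2. Compliance with the echocardiography protocol
3. Documented protocol deviations

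**Data sources in the Intervention characteristics row of Table 2 (three):**
1. Provider structured surveys
2. Frequency of protocol deviations
3. Registry completeness

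**Overlap:**
- Sources in the row that are also fidelity measures: 2 of 3 (items 2 and 3).
- Share of the Table 1 fidelity elements: 2 of 4.
- Share of the section 2.10 fidelity metrics: 2 of 3.
- Rows of Table 2 that name either quantity: 1 of 5.

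**Are the two uses kept apart?** They could be separated by period, by subset of forms, or by using only the reasons for deviations on the explanatory side. The article does none of these. Table 2 specifies the frequency of deviations, which is the part that coincides with the outcome.

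**Do the two quantities measure the constructs?** The row's constructs concern how complex the criteria seem, how clear the procedures are and how usable the registry is. A completeness rate or a deviation count is a downstream result that these may influence, along with much else. It is not a direct reading of any of them.

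**What independent information is left in the row?** Only the provider survey. Section 2.9.1 sends it at 12 months to one doctor and one nurse at each facility, so the maximum is 2 × 11 = 22 respondents, two per facility.

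**The case against.** The strongest reply is that CFIR is applied here only as an interpretive lens. Section 2.10 calls the analyses descriptive, disclaims formal between-facility comparison and rules out multilevel integration of the data sources. No model has fidelity on one side and these determinants on the other. That stands, and it limits the harm. It does not remove it: the row's stated role is still explanatory, and an explanation in words that uses the outcome as its own cause is no more informative than one in numbers.

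A second reply is that deviation records carry more than a count. Section 2.6.2 has deviations and contextual constraints documented in detail and reviewed monthly, and Table 1 records their nature as well as their frequency. This also stands. Recorded reasons are legitimate determinant data, and the fix keeps them.

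A third reply is that a statistical analysis plan or full protocol may settle the matter. This carries little weight, because the article does not leave the matter open: it names both the overlapping sources and the explanatory role.

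A reader might also infer more than the article supports:
- *That facilities will be rated on the CFIR constructs, and that a perfect association across the 11 facilities follows.* The article plans no such rating and no such association.
- *That the whole determinant objective is circular.* The overlap concerns two sources in one row. The adoption half of the objective, the survey in the same row and the other four rows are not shown to be affected.
- *That the Implementation process row has the same fault, because it uses the cardiologist over-read form.* Section 2.7 describes cardiologists giving feedback on image quality, so that form may simply be the record of that feedback. The article does not say that its image-adequacy results are the determinant.

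**Conclusion.** The point holds for the Intervention characteristics row of Table 2, and for the mention of deviation documentation in the text of 2.9 in so far as it means counts. Two of the row's three sources are fidelity outcomes, so for those two sources the row cannot say why fidelity varies. The harm is to the interpretation of one secondary objective. No primary outcome, estimate, test or error rate is affected.

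The conclusion rests on reading registry completeness and deviation frequency as the same quantities in Table 1, section 2.10 and Table 2. The near-identical wording supports that reading, and nothing in the article distinguishes them. The correction is small and worth making, because the plan as written would let the outcome stand as its own explanation.

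**What to change.** 1. In Table 2, Intervention characteristics row, remove deviation frequency and registry completeness from the data sources. Keep both as fidelity outcomes only, as in Table 1 and section 2.10.
2. In their place, list the provider survey items on complexity of the criteria, clarity of the procedures and registry usability, together with the documented reasons for deviations and the barriers recorded in the monthly check-in notes.
3. In the text of 2.9, change the reference to documentation of protocol deviations so that it means the recorded reasons and not the counts.
4. Add a sentence stating that this row is interpreted against fidelity measured separately.

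The cost is one table cell and a sentence or two of section 2.9. The surveys and monthly notes are already planned. The article does not show the survey items, but Table 2 already assigns these constructs to the survey, and it goes out only at 12 months, so there should be room to confirm that they are covered.

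Two limits should be stated. The survey part rests on one doctor and one nurse per facility, at most 22 respondents. Reasons for deviations exist only where deviations were recorded, so they should be read for content and not for number; counting them would bring the overlap back.

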#### Data sources

2.9.1

Data sources include facility clinical records, REDCap clinical data, provider and hospital superintendent surveys, and monthly monitoring reports with site-based study leads.

Facility clinical records: We will examine the routine paper-based clinical forms that exist in the facilities. We will examine background data on participants, as well as monthly records for participants who are positive for ARF. At the end of the program, researchers will hand search clinical forms to extract relevant data.

REDCap clinical data: Three types of REDCap clinical data will be used for this study.
When a suspected case is referred to a participating facility, the study encounter and suspected diagnosis will be recorded in REDCap.If the case screens positive for ARF, their echocardiogram will be reviewed by a Kathmandu-based cardiologist who will report their echocardiographic findings in REDCap.Per study protocol, at three study points (3, 6, and 12 months) patients diagnosed with ARF will be monitored for progress. These visits will be conducted using REDCap forms.Provider surveys: Surveys will be distributed at 12 months to all providers (one doctor and one nurse at each facility). Surveys will consist of a mix of multiple choice, Likert-scale and free text questions. These will be conducted in a mix of English and Nepali and will be conducted through Google forms.

Hospital superintendent surveys: Surveys will be distributed at 12 months to the superintendent in charge of each facility enrolled in this study. Surveys will consist of a mix of multiple choice, Likert-scale and free text questions. These will be conducted in a mix of English and Nepali and will be conducted through Google forms.

Monthly monitoring reports: Once a month, a central researcher from KIOCH will hold a “monthly check-in” with each of the 11 site-based study leads. These free-form discussions will cover barriers and solutions encountered over the past month, as well as number of cases, perceptions of case mix, and any questions that have arisen. These check-ins will not have audio recording but the KIOCH researcher will take detailed notes.

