#### Clinical evaluation workflow

2.6.2

ARF cases will be diagnosed if children meet 2015 modified Jones criteria (13) for high-risk populations. Nurses and physicians at participating facilities will confirm the diagnosis through laboratory tests, physical examination, and echocardiography. ARF diagnostic criteria included in SOPs and REDCap registry forms guide providers in confirming diagnostic criteria for enrollment.

Cases that are determined to be likely ARF are entered into the registry and their echocardiograms are uploaded for review by cardiologists. There are several participating cardiologists at tertiary care facilities in the capital city of Kathmandu who will provide diagnostic support and clinical advice as requested by study clinicians. Recruitment and follow-up will occur continuously, with structured follow-up visits scheduled at 3, 6, and 12 months post-enrollment for each ARF patient. Children requiring penicillin prophylaxis will be reviewed clinically in accordance with national follow-up guidelines. Follow-up will occur at the closest participating facility to the child's residence.

At each participating site, implementation is led by a designated clinical team comprising a physician, staff nurse, and laboratory technician. This team is responsible for application of ARF diagnostic criteria, echocardiographic assessment, registry documentation, and coordination of follow-up care.

Training was held by KIOCH in November 2025 during which SOPs for recruitment, ARF diagnostic criteria, and echocardiography protocols were reviewed with all providers and distributed. All facilities are expected to adhere to centrally defined SOPs and any deviations or contextual constraints will be documented in detail and reviewed during monthly monitoring and quality assurance meetings with the central KIOCH team.

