#### ARF diagnostic criteria

2.6.3

The 2015 modified Jones criteria (13) for high-risk populations will be used. The diagnosis of ARF is made if two major or one major and two minor criteria are met along with the evidence of streptococcal infection. If ARF is thought to be a recurrent episode, three minor criteria can be used to make the diagnosis. Major criteria include presence of carditis, mono- or polyarthritis, polyarthralgia, chorea, erythema marginatum, and subcutaneous nodules. Minor criteria include monoarthralgia, fever ≥38.0 °C, elevated inflammatory markers: ESR ≥30 mm/h and/or CRP ≥3.0 mg/dL, or prolonged PR interval on ECG. Prolonged PR interval is counted as a minor criterion only if carditis is not being used as a major criterion. There must be evidence of preceding group A streptococcal infection which is required for all except isolated chorea or indolent carditis. Antistreptolysin O Titer (ASOT) testing is provided to all facilities by the PRIMA study and will be the most common GAS antibody test used, though anti-DNase B titer, positive throat culture for GAS, and positive rapid antigen detection testing for GAS can also be used.

Carditis may be clinical or subclinical. Subclinical carditis is defined by Doppler echocardiographic evidence of pathological mitral or aortic regurgitation and morphologic changes as detailed in the 2023 World Heart Federation guidelines for the echocardiographic diagnosis of RHD (14). Echocardiographic assessments are performed using standardized imaging checklists which specifically include the criteria for pathological regurgitation and morphologic change. Echocardiograms are all uploaded for central review by cardiologists to support diagnostic consistency and fidelity. Kathmandu-based cardiologists serve as the final interpretive authority for echocardiographic findings, consistent with specialist referral practice within Nepal's health system. All clinics are equipped with a cardiac ultrasound machine.

Cases in which diagnostic criteria are not clearly met are reviewed by a study cardiologist, and children may be classified as suspected or probable ARF when appropriate. Diagnostic classification may be updated over time as additional clinical, laboratory, or echocardiographic information becomes available during follow-up, which reflects real-world practice.

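### The article conflicts on whose echocardiograms are read centrally, and does not keep the final-diagnosis rule out of diagnostic concordance

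*Protocol article*

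**What the plan says.** Three sections of the Protocol article describe who receives central echocardiographic review.

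- Section 2.6.2 (Clinical evaluation workflow): "Cases that are determined to be likely ARF are entered into the registry and their echocardiograms are uploaded for review by cardiologists".
- Section 2.9.1 (Data sources): "If the case screens positive for ARF, their echocardiogram will be reviewed by a Kathmandu-based cardiologist".
- Section 2.6.3 (ARF diagnostic criteria): "Echocardiograms are all uploaded for central review by cardiologists to support diagnostic consistency and fidelity". The same section adds: "Cases in which diagnostic criteria are not clearly met are reviewed by a study cardiologist".

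Section 2.6.3 also fixes the standing of the central readers: "Kathmandu-based cardiologists serve as the final interpretive authority for echocardiographic findings". It lets a child's classification change as further clinical, laboratory or echocardiographic information arrives.

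The last row of Table 1 (Section 2.8) lists "Diagnostic concordance with central cardiologist review" as an exploratory care-process indicator. The text after the table describes these indicators as covering "accuracy and timeliness of diagnosis, linkage to follow-up care, and follow-up completion over time". Section 2.10 names concordance with central review among the patient-level summaries, and the next sentence reads: "In cases where initial diagnosis is unclear and reclassification occurs, final diagnoses will be used where possible". Neither place gives a denominator for concordance, or says whether the site's initial or final assessment enters it.

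**The concern.** Two things determine what the concordance figure can mean.

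The first is who is read. If a central read is made only when the site thinks ARF is likely or present, no one checks the echocardiograms of children the site clearly called negative. Agreement among site-positives shows how often a positive call is confirmed and says nothing about missed cases. Missed ARF is the problem that motivates the programme, and Section 2.8 counts accuracy of diagnosis among the things these indicators describe. A later analysis plan cannot recover reads that were never made. Sites that follow different sections would also have different denominators, while Section 2.10 reports results by facility.

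The second is which diagnosis is compared. Where an unclear case is reclassified, the final diagnosis may already incorporate the cardiologist's read. Setting it against that same read makes the comparison partly circular, in the cases where disagreement is most informative.

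**Working it through.** The article states no concordance figure, sample size or expected agreement, so there is nothing to reproduce. The check is a reading of the text, followed by an illustration on assumed counts.

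**Step 1: the sections side by side.**

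| Section | Whose echocardiogram is reviewed |
|---|---|
| 2.6.2 | cases judged likely ARF |
| 2.9.1 | cases that screen positive |
| 2.6.3 | all echocardiograms; unclear cases also go to a study cardiologist |

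The unclear-case provision extends review beyond site-positives but does not reach clear site-negatives. Only the statement in 2.6.3 that all are uploaded does that.

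**Step 2: what each rule lets one estimate.** Cross-classify site call by central read: a = both positive, b = site positive and central negative, c = site negative and central positive, d = both negative, N = a + b + c + d.

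- Site-positives only: agreement = a/(a + b). Cells c and d are unobserved.
- All read: agreement = (a + d)/N, and the share of centrally positive children whom the site also called positive = a/(a + c).

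Assumed counts (none are in the article): N = 200, a = 34, b = 6, with c varied and d = 160 − c. The illustration has no separate unclear group.

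| c | Site-positives only, 34/40 | All read, (34 + d)/200 | Site capture, 34/(34 + c) |
|---|---|---|---|
| 0 | 85.0% | 97.0% | 100% |
| 2 | 85.0% | 96.0% | 94.4% |
| 5 | 85.0% | 94.5% | 87.2% |
| 10 | 85.0% | 92.0% | 77.3% |
| 20 | 85.0% | 87.0% | 63.0% |

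The restricted figure does not move while site capture falls from 100% to 63.0%.

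**Step 3: effect of the final-diagnosis rule.** Let r be the share of the b = 6 discordant cases whose initial call is replaced by a final diagnosis that follows the central reader. Among the 40 site-positives, agreement = (34 + 6r)/40.

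| r | Agreement |
|---|---|
| 0 | 85.0% |
| 0.25 | 88.75% |
| 0.50 | 92.5% |
| 0.75 | 96.25% |
| 1 | 100% |

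The rule covers only unclear cases that are reclassified, so r cannot exceed the share of discordant cases that meet both conditions.

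**The case against.** A reader might infer that the plan defines concordance on site-positive cases only. It does not. Sections 2.6.2 and 2.9.1 describe workflow and data sources, neither uses a restrictive word such as only, and no section gives a denominator. A condensed article may leave that denominator to a fuller document. Section 2.6.3 points towards review of everyone, and if it governs, children with an echocardiogram whom the site missed would be visible.

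A reader might also infer that agreement in reclassified children is perfect by construction. The text does not support that. The rule applies to unclear, reclassified cases and is qualified further in "In cases where initial diagnosis is unclear and reclassification occurs, final diagnoses will be used where possible". Reclassification can come from a late laboratory result or evolving clinical signs. The Kathmandu cardiologists have the last word on echocardiographic findings, while the ARF diagnosis also rests on clinical and laboratory criteria. A final diagnosis is therefore not the same thing as the central read.

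Nor does restricting review to positives necessarily flatter the figure. In the illustration the restricted agreement of 85.0% lies below the all-read agreement in every row. The difficulty is that it answers a different question.

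Finally, the indicator is exploratory and descriptive, is expressly outside the Proctor outcomes, and has no success threshold attached. The suspected diagnosis and the cardiologist's findings are already entered in REDCap separately, so much of the needed information exists.

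All of this stands and limits the point. It does not remove the conflict over whose echocardiograms are read, or supply the missing exemption for concordance in Section 2.10.

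**Conclusion.** The point holds in a limited form. The article gives incompatible accounts of who is centrally read. Under Sections 2.6.2 and 2.9.1, concordance can be computed only among likely or site-positive cases, plus any unclear cases reviewed under Section 2.6.3. Among site-positives it is a confirmation rate, and clear site-negatives go unchecked. Section 2.10 leaves concordance exposed to the final-diagnosis rule, so agreement in reclassified cases can be inflated. On the assumed counts the inflation runs from nothing to 15 percentage points (85.0% to 100%), and the upper end requires every discordant case to be replaced by a diagnosis that follows the central reader.

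The sizes depend entirely on those assumed counts, and they measure agreement with the central echocardiographic read, not with true ARF status. Even a read of every echocardiogram would not reveal missed ARF without carditis. Severity is minor to moderate: what the indicator can show changes, but acceptability, feasibility and adoption do not depend on it.

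**What to change.** 1. Reconcile Sections 2.6.2 and 2.9.1 with Section 2.6.3, so that one statement says whose echocardiograms are centrally read.
2. In Section 2.10, define concordance as the site's initial echocardiographic read, recorded before central review, against the central echocardiographic read. This compares like with like; the whole ARF diagnosis against an echocardiographic read would not.
3. Limit the final-diagnosis rule to diagnostic patterns and case counts.
4. If all echocardiograms are read, report agreement over all children with an echocardiogram. If only positive or likely cases are read, label the figure as central confirmation of site-positive cases, and do not present it as diagnostic accuracy.

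The cost is wording plus one recorded REDCap field for the site's read before central review. No reads are needed beyond those Section 2.6.3 already promises, and none are added if the indicator is relabelled. The downside is that agreement among reclassified cases may come out lower. Recruitment began in February 2026, so the reading rule and the field should be settled early: reads not made and initial calls not recorded are hard to reconstruct.
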